### **3.1 Primary Outcome** : The change of the Cobb angle

## 3.2 Secondary Outcome :

- (1) The change of the angle of trunk rotation, ATR ;
- (2) The changes in pelvic tilt angle during the gait cycle between baseline and the 6-month follow-up.
- (3) Engagement metrics of participants.
- (4) The population of AIS patients with progression and improvement of Cobb angle of the major curve

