## 3.3 The definition of outcomes

All subjects will undergo baseline measurements at the Department of Rehabilitation, Peking Union Medical College Hospital. After a 6-month intervention, all participants are required to return to the hospital for a 6-month follow-up assessment. The primary outcome measure is the change in the Cobb angle of the primary curve between baseline and the 6-month follow-up. The Cobb angle will be measured on standing radiographs by two physical therapists (PTs) who will determine the angle between the most tilted vertebrae at the upper and lower ends of the curve. The final Cobb angle will be the average of the two measurements. Secondary outcomes are listed in Table 5.

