### Study secondary outcomes (clinical and engagement)

| Outcome measure                                                                                  | Description                                                                                                                                                                                                                                                                                                                                                                                    |
|--------------------------------------------------------------------------------------------------|------------------------------------------------------------------------------------------------------------------------------------------------------------------------------------------------------------------------------------------------------------------------------------------------------------------------------------------------------------------------------------------------|
| The population of AIS patients with progression and improvement of Cobb angle of the major curve | The research team defines a reduction in the primary curve Cobb angle of 0° to 5° as "mild improvement," a reduction of more than 6° as "substantial improvement," and an increase in the primary curve Cobb angle as "progression." This study analyzed the populations of AIS patients in the DCG and CIG groups in terms of progression, "mild improvement," and "substantial improvement." |
| The improvement in the angle of trunk rotation (ATR)                                             | To evaluate the improvement in vertebral rotation at the spinal level in patients with AIS (Idiopathic Scoliosis) based on ATR (Angle of Trunk Rotation) improvement at baseline and 6-month follow-up, the following procedure is conducted:                                                                                                                                                  |

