|                                                                                                           |                                                                                                                                                                                                                                                                                                                                                                                                                                                                                                                                                                                                                                                                                                       |
|-----------------------------------------------------------------------------------------------------------|-------------------------------------------------------------------------------------------------------------------------------------------------------------------------------------------------------------------------------------------------------------------------------------------------------------------------------------------------------------------------------------------------------------------------------------------------------------------------------------------------------------------------------------------------------------------------------------------------------------------------------------------------------------------------------------------------------|
|                                                                                                           | 
The subject is asked to stand with feet shoulder-width apart, and the examiner is seated behind the subject. The subject is instructed to slowly bend forward until the spinal deformity is most prominent, with the apex of the hump aligned with the examiner's line of sight. A scoliometer (Orthopedic Systems INC, Union City, California, USA) is placed on the spinous process at the apex of the curve, and the ATR angle is recorded.
                                                                                                                                                                                                                                                 |

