## **4.3 Statistical Method**

The distribution of continuous variables was assessed using the Kolmogorov-Smirnov test, followed by verification through histograms and Q-Q plots. Demographic data were presented as mean (standard deviation) for continuous variables and as number (percentage) for categorical variables. Baseline demographic characteristics and engagement metrics between groups were compared using independent samples t-test or Mann-Whitney U test for quantitative variables, and Chi-square test or Fisher's exact test for categorical variables.

The effects of each intervention on primary and secondary outcomes were evaluated based on the 6-month endpoint outcomes and the changes between baseline and 6 months. Both intention-to-treat (ITT) and per-protocol analyses were conducted for outcome assessment. Missing data were handled using multiple imputation by chained equations (MICE).

Receiver operating characteristic (ROC) curve analysis was employed to determine the minimal clinically important difference (MCID) for improvement in Cobb angle post-PSSE intervention at 6 months, which was identified as 3.50 degrees. However, Charalampidis A et al. defined treatment success in patients with moderate idiopathic scoliosis as no progression in scoliosis in individuals with a Risser grade  $\leq 4$  after 6 months of PSSE intervention.

The primary and secondary outcomes of this study were reported as mean, standard deviation (SD), and 95% confidence interval (CI). Given the assumption of normality, primary and secondary outcomes were evaluated using the independent samples t-test. The proportion of patients who exhibited disease progression or improvement in Cobb angle between the two groups was compared using the Chi-square test.

179 All analyses were conducted under a two-tailed hypothesis with an alpha level of  
180 0.05. Statistical analyses were performed using SPSS (version 23.0, SPSS Inc.,  
181 Chicago, Illinois, USA), and were carried out by a blinded statistician

182

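### As written, the trunk rotation (ATR) procedure yields one scoliometer reading per visit; averaging three would remove some avoidable variance from this secondary outcome at very little cost

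*Protocol*

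**What the plan says.** Protocol section 3.2 lists ATR first among the secondary outcomes, as a change: "The change of the angle of trunk rotation, ATR". The outcome table under section 3.3 refers to "improvement at baseline and 6-month follow-up", so there are two measuring visits.

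The same table gives the procedure. It fixes the patient's stance, and "the examiner is seated behind the subject". The patient bends forward until the deformity is at its most visible, and the scoliometer "is placed on the spinous process at the apex of the curve, and the ATR angle is recorded". Examiner, placement and angle are all in the singular. Nothing in the protocol mentions a second ATR reading, a second examiner or averaging for this outcome.

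For the Cobb angle, section 3.3 has two physical therapists measure the radiographs, and "The final Cobb angle will be the average of the two measurements".

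Section 4.3 evaluates outcomes both on the 6-month values and on the changes from baseline. Under the normality assumption, "primary and secondary outcomes were evaluated using the independent samples t-test". Testing is two-sided at 0.05.

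**The concern.** A scoliometer reading can depend on how far the patient bends and on where the instrument is set down. The procedure leaves the end of the bend and the apex to the examiner's eye. With one reading per visit, whatever error attaches to that reading goes in full into the standard deviation used by the t-test. It enters once for the 6-month value and twice for the change, because baseline and month 6 each bring their own error.

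What is at stake is precision. A real group difference in trunk rotation could be missed, or estimated with a wider interval than necessary, although the patient, the examiner and the instrument are already together at the visit. The rule also belongs in the data-collection procedure, because no later analysis can average readings that were never taken.

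**Working it through.** **Inputs from the protocol.** Two visits; one placement and one recorded angle per visit, read from singular wording; an independent-samples t-test, two-sided 0.05; 51 per group for analysis and 64 per group enrolled (section 4.4).

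**Not in the protocol.** Any ATR standard deviation, effect, reading error or power. The sample size in section 4.4 concerns the Cobb angle only, so there is no ATR figure to reproduce.

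**Assumptions.**
- q is the share of the single-reading change variance that is reading error; it is shown from 10% to 60%.
- ρ is the correlation between the errors of replicate readings at the same visit; it is shown at 0 and 0.5.
- Errors at the two visits are independent.
- The comparison starts at 80% power on single readings.

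**Variance of the ATR change.** Write V for the variance of true change and SEM for the standard error of one reading.

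- One reading per visit: V + 2·SEM²
- Mean of three readings per visit: V + 2·SEM²·(1 + 2ρ)/3

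With q = 2·SEM²/(V + 2·SEM²), averaging multiplies the change variance by

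f = 1 − q·[1 − (1 + 2ρ)/3]

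This is 1 − 2q/3 when ρ = 0, and 1 − q/3 when ρ = 0.5.

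**Power.** At 80% power and two-sided 0.05, the standardised difference is 1.960 + 0.842 = 2.802. After averaging, power = Φ(2.802/√f − 1.960).

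| q | f (ρ = 0) | Power (ρ = 0) | f (ρ = 0.5) | Power (ρ = 0.5) |
|---|---|---|---|---|
| 10% | 0.933 | 82.6% | 0.967 | 81.3% |
| 20% | 0.867 | 85.3% | 0.933 | 82.6% |
| 40% | 0.733 | 90.5% | 0.867 | 85.3% |
| 60% | 0.600 | 95.1% | 0.800 | 88.0% |

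Worked example for q = 60%, ρ = 0: f = 1 − 0.6 × 2/3 = 0.600 and √f = 0.775. Then 2.802/0.775 = 3.617, 3.617 − 1.960 = 1.657, and Φ(1.657) = 95.1%.

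The same powers result from the exact t-test at 51 and at 64 per group.

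**The 6-month values.** Here reading error contributes SEM² once. With W for the true spread between patients at month 6, its share is SEM²/(W + SEM²). This is smaller than q whenever W exceeds V/2. In that case the gain for this analysis is smaller than in the table.

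**Sensitivity to the inputs.** A separate check used the mean of two independent readings, 51 per group and an assumed group difference of 1.5 degrees. With SEM 0.5 and true-change SD 4 degrees, power moves from 46.2% to 46.8%. With SEM 2 and true-change SD 1.5 degrees, it moves from 65.8% to 85.8%. Depending on figures that the protocol does not give, the gain is therefore anything from trivial to material.

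**The case against.** Several points on the other side have force.

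- **The protocol does not say that only one reading is taken.** This stands: a single reading is inferred from singular wording, and repeats are not ruled out. But the procedure is spelled out in detail and nothing in it asks for a repeat. If the site already repeats readings, the remedy is one clarifying sentence.
- **A reader might infer that the protocol contradicts itself by averaging Cobb readings but not ATR readings.** The text does not support that. The Cobb angle is the primary outcome and the basis of the sample size, so more measuring effort there is an ordinary choice. The two steps also differ in kind: two therapists measuring radiographs average out reader error, whereas one examiner repeating the bend averages out variation between bends.
- **A reader might also infer that ATR ranks highest among the secondary outcomes because section 3.2 lists it first.** The outcome table lists it second, and the protocol states no hierarchy and no power target for ATR.
- **The size of the gain is assumed.** This stands, so no particular loss of power can be attributed to the plan. Consecutive readings by an examiner who remembers the previous value may well share error, which is why the correlated column belongs beside the independent one.
- **Averaging within a visit does not remove everything.** Day-to-day variation in posture remains, and so does any error the examiner repeats.
- **Requiring one examiner for both visits would constrain scheduling over six months.** This stands, and it is a reason to make it a preference only.

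**Conclusion.** The point holds as a minor, inexpensive improvement in precision. As written, the protocol takes one ATR reading per visit, and this leaves avoidable random error in the 6-month comparison (once) and in the change (twice). Random error of this kind does not by itself bias the group comparison, and it does not touch the primary outcome.

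The illustrated gain from averaging three readings starts at about 1 to 3 percentage points of power if reading error is 10% of the change variance. At a share of 60% it is about 8 points with correlated errors, or 15 points with independent errors. These figures rest on the assumed shares, correlations and 80% starting power, none of which the documents supply. The reading that the trial is losing a known or large amount of power on ATR goes beyond the text.

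**What to change.** In the ATR row of the secondary outcome table, state that:

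- at baseline and at month 6 the examiner takes three readings at the same spinal level, with the patient returning to upright between bends;
- all three readings are recorded, and their mean is the ATR for that visit;
- the same examiner is used at both visits where feasible, as a preference and not a requirement.

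The cost is a minute or two per visit, two more fields on the form and two more forward bends for the patient at each visit. No extra equipment, visit or radiation is needed. Keeping all three readings would also let the trial report its own within-visit reading error, which the protocol currently lacks.

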| 
The changes in pelvic tilt angle during the gait cycle between baseline and the 6-month follow-up.
 | 
Pelvic coronal plane asymmetry negatively impacts the gait of patients with AIS. The pelvic tilt angle during the gait cycle is measured using the MOVIT Gait System (Sensor Medica s.r.l., [name]). Changes in this angle from baseline to the 6-month follow-up are utilized to assess improvements in pelvic tilt. Four representative time points within the gait cycle are selected for analysis, corresponding to the minimum and maximum values during the stance phase, and the minimum and maximum values during the swing phase. The validity and reliability of the MOVIT Gait System have been established.
 |
| 
Engagement
                                                                                         | 
The assessment of engagement will be conducted through the following metrics: (i) adherence to home-based exercise performance, including the frequency of over-corrective exercises per week, the duration of over-corrective exercises per week, and the number of individuals in both groups who consistently practice self-correction exercises daily; (ii) dropout rates. Data for the DCG will be automatically collected by the HIRS system, while CIG data will be manually recorded by individuals or their patients.
                                                                                                                                                                 |

---

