The PSSE training consisted of daily self-correction exercises and over-correction exercises. The daily self-correction exercises were based on the SEAS methodError! Reference source not found., where therapists instructed AIS patients in specific three-dimensional corrective postures in the sagittal, coronal, and transverse planes, aiming to realign the spine to a neutral position. To enhance patient self-management of posture, PTs will require AIS patients to maintain the self-corrective posture during routine activities such as sitting, standing, and walking whenever possible. If patients are unable to actively control their posture continuously, they will be encouraged to utilize aids, such as insoles or cushions, to achieve passive correction. Given that the trial participants are students who spend

the majority of their day in a seated position, seated self-correction exercises formed a significant component of the daily training regimen. All AIS patients perform a minimum of 30 minutes of seated self-correction exercises daily for a duration of six months. The over-correction exercises were derived from the Schroth method. The over-corrective exercise protocols varies according to the PUMCH-SSE classification. During the over-correction training, patients' spines are compelled to maintain a neutral or even over-corrected position. All AIS patients engage in over-correction exercises for 30 minutes per day, at least five days a week, for a duration of six months. The PSSE training regimen, established based on the PUMCH-SSE classification, has been demonstrated to be effective for AIS patients.

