In this trial, individuals in the DCG group receive a single in-person PSSE training session under the guidance of physical therapists (PTs) in an outpatient setting. During this session, PTs will assist patients or their guardians in installing the HIRS system on their smartphones and provide instructions on how to utilize the system. Simultaneously, individuals with AIS will be required to promptly study educational videos and articles related to scoliosis to enhance their understanding of the conditionError! Reference source not found.. Following this session, individuals in the DCG group will complet home-based PSSE training through the HIRS system. The HIRS system automatically records individual PSSE training performance and engagement data, including the number of sessions and duration of training.

In the Conventional Intervention Group (CIG), individuals will receive three 90-minute in-person training sessions per month, under the guidance of PTs, during the first three months, with additional guidance sessions provided as needed. During these sessions, patients or their guardians are required to record the entire PSSE instructional process on video and received printed PSSE exercise materials. Subsequently, patients with scoliosis will complete the six-month PSSE training regimen at home using these videos and materials.

Figure 2. Example of the HIRS system.

[figure not shown]

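### Self-correction adherence is listed only as a headcount of patients who practise daily, with no threshold, while over-correction adherence keeps a weekly scale; the cut discards information at a cost that depends on the adherence pattern

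*Protocol*

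**What the plan says.** The Engagement row of the secondary outcome table in Protocol 3.3 names three adherence measures. Two concern over-correction and are quantitative: "the frequency of over-corrective exercises per week, the duration of over-corrective exercises per week". The third concerns self-correction and is a count of patients: "the number of individuals in both groups who consistently practice self-correction exercises daily". The protocol does not say how many days, over what period, make a patient *consistent*.

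Section 4.3 compares quantitative engagement metrics by t-test or Mann-Whitney U test, and uses "Chi-square test or Fisher's exact test for categorical variables". The self-correction headcount therefore falls under the categorical tests.

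Section 6.3 describes the two parts of the programme: "The PSSE training consisted of daily self-correction exercises and over-correction exercises". It prescribes the first part as follows: "All AIS patients perform a minimum of 30 minutes of seated self-correction exercises daily for a duration of six months".

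On data capture, section 6.3 says of the digital arm (DCG): "The HIRS system automatically records individual PSSE training performance and engagement data, including the number of sessions and duration of training". For the conventional arm (CIG), the Engagement row says only "while CIG data will be manually recorded by individuals or their patients".

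**The concern.** The Background (section 1) motivates the trial by poor home adherence and by patients not forming habits of daily self-management. Of the adherence measures listed, self-correction is closest to that rationale, yet it has the coarsest scale. Once patients are split into yes and no, someone just short of the threshold counts the same as someone who never practised. A real difference in practice between the arms can then go undetected.

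The missing threshold adds a second problem. The result depends strongly on where the cut falls, and the protocol does not fix it in advance.

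**Working it through.** **Plan's own figure.** There is none to reproduce. The protocol gives no expected rate, effect, SD or power for this metric.

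**Inputs from the protocol.** 51 evaluable patients per group (4.4) and two-sided alpha 0.05 (4.3). The 51 is taken as given; how it was derived does not matter here.

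**Assumptions.** The standardised adherence difference d is 0.5, 0.565 or 0.667. The middle value gives about 80% power on the full scale. Six months is taken as 26 × 7 = 182 days.

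**Step 1, normal measure.** Full-scale power is that of the two-sample t-test with 100 degrees of freedom and non-centrality d × √(51/2). For the cut, let p0 be the share of controls who qualify. The digital-arm share is then p1 = 1 − Φ(z − d), where z = Φ⁻¹(1 − p0). Example: p0 = 0.20 and d = 0.565 give p1 = 0.391. Power of the uncorrected Chi-square test is summed exactly over the two binomial distributions.

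| d | t-test, full scale | p0 = 5% | 10% | 20% | 30% | 50% |
|---|---|---|---|---|---|---|
| 0.5 | 70.6% | 26.5% | 36.3% | 46.9% | 52.1% | 52.5% |
| 0.565 | 80.7% | 33.9% | 45.5% | 57.1% | 62.7% | 61.9% |
| 0.667 | 91.5% | 47.1% | 60.8% | 72.0% | 77.3% | 75.0% |

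The smallest loss in the table is 91.5 − 77.3 = 14 points. The largest is 80.7 − 33.9 = 47 points. A control share of 40% is marginally kinder (78.2% at d = 0.667, a loss of 13).

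**Step 2, skewed day counts.** Each patient's daily probability is drawn from a beta distribution with mean m and concentration c (parameters mc and (1 − m)c). Days practised are then binomial out of 182. There are 51 patients per group and 6,000 runs, so the simulation error is below 0.7 points.

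| Means, c | t-test | Mann-Whitney | Cut at 80% of days | 90% | 95% | Every day |
|---|---|---|---|---|---|---|
| 60% v 72%, c = 4 | 79% | 79% | 61% | 51% | 35% | 0.2% |
| 80% v 88%, c = 4 | 69% | 80% | 52% | 66% | 67% | 48% |

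In the second row, cuts at 90% and 95% lose 68.8 − 66.4 and 68.8 − 66.8, about 2-3 points against the t-test. Against Mann-Whitney they lose 80.0 − 66.4 and 80.0 − 66.8, about 13-14 points. With c = 6 and the same means, the losses at these cuts are about 5-7 and 12-13 points.

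**Step 3, the every-day reading.** If a patient practises on any given day with independent probability q, the chance of qualifying is q^182:

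- q = 0.95: 0.009%
- q = 0.98: 2.5%
- q = 0.99: 16%
- q = 0.995: 40%

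On this reading hardly any patient qualifies unless that patient's own daily adherence is about 99% or more. Variation between patients softens this. In the second row of Step 2, about 4% and 14% of patients qualify; in the first row, 0.1% and 1%.

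**The case against.** **The scale may not be exclusive, and a SAP may say more.** The Engagement row introduces its metrics as examples of what adherence includes, and a SAP could define *consistently* or add summaries. The missing definition alone would therefore not be a finding, and a SAP could close the question of a late-chosen threshold. But the protocol itself names the headcount as the only self-correction measure, beside a quantitative measure for the companion exercise. That choice is made in this document.

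**The cut is not arbitrary.** Daily practice is the prescribed regimen, so counting patients who meet it is natural and easy to read. This stands, and is a reason to keep the count as a description.

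**A reader might infer a fixed minimum power loss, or a metric that must sit near zero.** The documents support neither. No adherence effect or rate is stated, and Step 2 shows a loss of only 2-3 points against the t-test in one plausible pattern. The floor appears only if *consistently* means every single day. With means of 80% v 88%, c = 4 and a 90% cut, 39% and 61% of patients qualify, which is mid-range.

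**A reader might also infer that self-correction days and minutes are already recorded in both arms.** The app logs training as a whole in the digital arm, "including the number of sessions and duration of training", without naming self-correction separately. The content of the conventional arm's manual record is not stated. Part of self-correction is posture held during ordinary activities, which need not appear as an app session.

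**The consequence is limited.** This stands too. It is one component of one secondary outcome that the trial was not sized for.

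**Conclusion.** The point holds as a cheap improvement to a secondary outcome. The protocol puts self-correction adherence on an undefined yes/no scale while keeping over-correction on a weekly scale. In every scenario examined the cut had less power than the full-scale comparison.

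The size rests on assumptions the protocol does not supply:

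- about 14 to 47 points for a normal measure with 51 per group and 70-92% full-scale power;
- about 13-14 points against Mann-Whitney and 2-3 against the t-test for high, skewed adherence (means 80% v 88%, concentration 4, cut at 90-95% of days);
- almost complete loss if every day is required and adherence is moderate (60% v 72%).

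No single figure should be quoted as the loss. The primary Cobb-angle comparison is not touched.

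**What to change.** In the Engagement row of the secondary outcome table, define self-correction adherence as the number of days per week on which it was practised, averaged over the six months. Compare it between arms by the t-test or Mann-Whitney U test that section 4.3 already names. Keep the number of patients practising daily as a descriptive count, with its threshold written down before the data are seen.

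State that both arms record the same daily item: whether self-correction was practised that day. In the digital arm, confirm that the app can separate self-correction from other training. Add minutes per week only if both arms record minutes, because a daily tick does not yield them.

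The cost is a change of wording in the table, one diary line for conventional-arm families, and descriptive status for the headcount. Treatment and sample size do not change. The existing difference between automatic recording in one arm and manual recording in the other remains, and should be noted when the result is interpreted.

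### Exercise adherence is logged by the app in the DCG and hand-recorded in the CIG, then tested between arms, so recording method and arm cannot be separated

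*Protocol*

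**What the plan says.** Section 3.2 of the Protocol lists "Engagement metrics of participants" as a secondary outcome. The table of secondary outcomes under Section 3.3 breaks this into adherence to home exercise and dropout. The adherence part has three measures. Two are weekly quantities, given as "the frequency of over-corrective exercises per week, the duration of over-corrective exercises per week". The third is a count of people, defined in the table as "the number of individuals in both groups who consistently practice self-correction exercises daily". Besides adherence, the outcome includes a second part, listed as "ii) dropout rates".

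The same row fixes the data source for each arm: "Data for the DCG will be automatically collected by the HIRS system, while CIG data will be manually recorded by individuals or their patients". The last word is presumably a slip for parents.

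Section 4.3 plans a formal comparison: "engagement metrics between groups were compared using independent samples t-test or Mann-Whitney U test for quantitative variables", with chi-square or Fisher's exact tests for categorical variables, all two-sided at 0.05. Section 4.5 says that patients and therapists cannot be blinded. The Protocol describes no measure of adherence common to both arms, no check of the CIG record, and no caveat about the difference in source.

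**The concern.** A between-arm test of adherence is informative only if adherence is measured in the same way in both arms. Here every DCG value comes from an automatic log and every CIG value from a manual entry by an unblinded patient or family member. Randomisation balances the patients but not the instruments. A blinded statistician and a well-chosen test cannot help either, because no patient in one arm is measured by the other arm's method.

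This matters because adherence is part of the trial's rationale. The Background attributes poor results of the traditional model to incomplete home programmes and presents digital tools as a way to improve adherence. A significant engagement result would be read as support for that mechanism, and a null result as evidence against it. Under the plan as written, neither reading would be safe.

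**Working it through.** **Where the two records differ, from the text of the Protocol**

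- *DCG.* Section 6.3 says the app records training performance and engagement, including number of sessions and their duration. Patients must go through the app each time they train. A missed exercise triggers a reminder and a therapist contact, so the log is also part of the intervention.
- *CIG.* The record is manual. Its form, timing and checking are not described, and nothing comparable to the reminder is attached to it.
- *Daily self-correction.* The measure counts people who practise consistently. The Protocol does not say how that is scored from an app log and how from a manual record.

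**Is there a planned figure to reproduce?** No. The Protocol gives no expected value, SD or power for engagement. The sample size in Section 4.4 concerns the Cobb angle only. What follows is illustration.

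**Inputs from the Protocol**

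- Prescribed over-correction exercise (Section 6.3): 5 days × 30 min = 150 min/week, as a minimum, in both arms.
- Arm sizes (Section 4.4): n = 51 evaluable or 64 enrolled per arm.
- Alpha (Section 4.3): 0.05 two-sided, critical value 1.96.

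**Assumed inputs**

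- True adherence is equal in both arms at 150 min/week.
- One arm's record is off by 10%, 20% or 30%, that is 15, 30 or 45 min/week. The sign does not alter the probabilities.
- The SD is 30, 50 or 75 min/week.

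**Weekly duration.** The probability of a significant difference when behaviour is identical is approximately Φ(δ / (σ√(2/n)) − 1.96), where δ is the recording bias.

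Worked case, σ = 50, δ = 15:
- n = 51: 50√(2/51) = 9.90; 15/9.90 = 1.515; Φ(1.515 − 1.96) = Φ(−0.445) = 0.33.
- n = 64: 50√(2/64) = 8.84; 15/8.84 = 1.697; Φ(1.697 − 1.96) = Φ(−0.263) = 0.40.

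All cases, as n = 51 to n = 64:

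| Assumed SD (min/week) | Bias 15 min (10%) | Bias 30 min (20%) | Bias 45 min (30%) |
|---|---|---|---|
| 30 | 0.71–0.81 | over 0.99 | over 0.99 |
| 50 | 0.33–0.40 | 0.86–0.92 | over 0.99 |
| 75 | 0.17–0.20 | 0.52–0.62 | 0.86–0.92 |

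**Daily self-correction (proportion).** With p₁ the true proportion in both arms, p₂ the over-recorded proportion in one arm and p̄ their mean, the probability is approximately Φ([(p₂ − p₁)√n − 1.96√(2p̄(1 − p̄))] / √(p₁(1 − p₁) + p₂(1 − p₂))).

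Worked case, p₁ = 0.60, p₂ = 0.70, n = 51: (0.714 − 1.322)/0.671 = −0.906, and Φ(−0.906) = 0.18.

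- True 60%: 10 points of over-recording gives 0.18–0.22; 20 points gives 0.60–0.70.
- True 50%: 0.17–0.20 and 0.54–0.64.

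The nominal rate in every case is 0.05.

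**The reverse case.** A recording bias can also hide a real difference. If true adherence differed by 30 min/week and the records were biased by 30 min/week the other way, the expected observed difference would be 30 − 30 = 0. With SD 50, the chance of a significant result would fall from 0.86–0.92 to about 0.05.

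**The case against.** The strongest reply is that the confounding is real but its consequences are limited, and that several stronger readings go beyond the text. Most of this stands.

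- **Per-protocol analysis.** A reader might infer that the per-protocol Cobb angle result is biased as well, since Section 4.3 says "Both intention-to-treat (ITT) and per-protocol analyses were conducted for outcome assessment". The Protocol does not say that membership depends on adherence records, and that definition may sit in an SAP that is not shown. The problem would carry over only if membership were defined from these records.
- **Direction.** A reader might infer that self-recording flatters the CIG. The Protocol does not establish this. Manual records can overstate exercise or miss it, and the app can miss exercise done outside it. Particular mechanisms, such as video left running, zeros logged after dropout or records lost by families, are not described in the Protocol.
- **Self-correction.** Patients are asked to "maintain the self-corrective posture during routine activities such as sitting, standing, and walking whenever possible", and a reader might conclude that the app cannot see self-correction at all. But Section 6.3 also prescribes a countable daily seated exercise, treats self-correction as part of the training, and requires the app to be opened for each training session. The log may well capture it. What remains is that scoring from the two sources is not described.
- **Scope.** Dropout is also an engagement metric and does not plausibly depend on log or manual record. The hypotheses and the primary outcome concern the Cobb angle only.
- **Size.** The biases, SDs and proportions above are assumed.

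Two further replies carry less weight. The multiple imputation planned in Section 4.3 addresses missing values, not values recorded differently by arm. And although the app log may be the more objective record, an objective measure in one arm alone does not make a comparison valid.

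**Conclusion.** The point holds for the three adherence measures. As planned, their between-arm tests compare behaviour and recording method together, and no analysis of the planned data can separate the two. The direction of bias is unknown. Its size can only be illustrated: across the assumed cases for weekly duration, the chance of a significant result with equal true adherence runs from 0.17 (10% bias, SD 75, 51 per arm) to over 0.99, against a nominal 0.05.

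The consequence is an uninterpretable comparison within one secondary outcome, and weak ground for any adherence-based explanation of the main result. The intention-to-treat Cobb angle comparison and the dropout comparison are untouched. The point deserves correction because the remedy is cheap and a common measure cannot be created after the data are collected.

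**What to change.** Collect the same short weekly self-report in both arms: number of sessions, minutes, and daily self-correction yes or no. Use the same form, timing and mode of delivery. Sending it through the app to the DCG alone would bring back a difference of mode. Base the between-arm comparison on this report. Keep the app log as supplementary DCG-only data and as a check on DCG self-report.

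If this cannot be added, report the three adherence measures descriptively by arm, without p-values, and state the difference in data source wherever they appear. Dropout can still be compared formally.

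Should the per-protocol set need an adherence criterion, in-person attendance would not be a neutral basis. Section 6.3 plans one such session in the DCG and three per month for three months in the CIG (Section 6.2 describes three sessions, and the two passages need to be reconciled), so an attendance rule would select differently by arm.

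The cost is a short weekly form for the 64 DCG families and a standard form in place of the existing manual record in the CIG. There is a small extra burden and a mild prompting effect in the DCG. Self-report also remains unblinded, and DCG families know that the app monitors them, so a common form reduces the difference between arms but does not guarantee its removal. The descriptive fallback costs nothing beyond the p-values.
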